##### Adverse events

2.4.2.6

Adverse events will be collected from the time informed consent is signed until the end of the 4-month intervention. Evaluation of potential adverse events will be performed during each visit and phone call by study investigators. The type, severity, seriousness, duration and relationship of the adverse events to study formulas will be recorded and listed by system-organ class and preferred term according to the Medical Dictionary for Regulatory Activities (MedDRA) glossary. The intervention with the two formulas is considered low risk and no significant adverse events are expected. During the period where parents are offered a post-study access to the assigned formula, no data will be proactively collected, however adverse events can be spontaneously reported by parents.

#### Study schedule

2.4.3

Study visits will take place on-site at enrollment and 1, 2, 3, and 4 months post-enrollment. Additionally, a phone call to the caregivers will be made on day 7 after enrollment to inquire about the infant’s health status and the occurrence of any adverse events. A detailed overview of the study procedures can be found in Table 2.

**Table 2 tab2:** Study visits and assessments.

Visit or phone call number	V0	C1	V1	V2	V3	V4
Infant age	≤ 8 mo	V0 + 7 days (±3 days)	V0 + 1 mo (±7 days)	V0 + 2 mo (±7 days)	V0 + 3 mo (±7 days)	V0 + 4 mo (±7 days)
Informed consent	X					
Assign subject number	X					
Inclusion/exclusion criteria	X					
Physical examination	X					X
Medical history	X					
Parent / household characteristics	X					
Randomization	X					
Weight and Length	X		X	X	X	X
Head Circumference	X					X
Tibia and femur length	X					X
Infant Gastrointestinal Symptom Questionnaire (IGSQ)	X	X	X	X	X	X
Daily gastrointestinal tolerance questionnaire	→	→ |				
Retrospective 1-day stool record	X					
3-day stool diary				X		X
CoMiSS Questionnaire	X		X	X	X	X
Food Allergy Quality of Life Questionnaire	X					X
Food Allergy Self-Efficacy Questionnaire	X					X
ITQOL-SF 47	X					X
Formula compliance		X	X	X	X	X
Parent and child product liking						X
Dietary intake assessment (24-h recall)	X			X		X
Formula dispensation and accountability	X		X	X	X	X
Cow’s milk elimination diet	→	→	→	→	→	→
Concomitant medication/diet record	→	→	→	→	→	→
Adverse event record	→	→	→	→	→	→

C, call; CoMiSS, Cow’s Milk-related Symptom Score; ITQOL-SF 47, Infant and Toddler Quality of Life Questionnaire-Short Form; Mo, months; V, visit.

#### Data analysis

2.4.4

The analyses of this study will adhere to the recommended guidelines outlined in the CONSORT 2022 statement for reporting outcomes in clinical trial reports (36).

The Intention-to-Treat (ITT) analysis population will include all randomized infants. The full analysis set (FAS) will consist of a subset of subjects from the ITT with available weight-for-age z-scores at baseline and 4 months and available measurements for all other covariates included in the model. The Per Protocol (PP) set will include all infants from the FAS having no protocol deviations impacting the primary endpoint, nor documented concomitant medication intakes impacting the primary endpoint, nor violated eligibility criteria. In particular, infants that are non-compliant to feeding interventions will be excluded from the PP set. The analysis in aforementioned populations will be conducted using the assigned intervention. The safety analysis set (SAF) will consist of all infants in the ITT population with documentation of at least one administration of study product, analyzed according to the product received irrespective of the randomization assignment. The primary and secondary endpoints will be analyzed in both FAS and PP populations.

Descriptive statistics will be calculated and tabulated for all categorical and continuous variables by visit and feeding group. The primary endpoint of weight-for-age z-score after 4 months of intervention will be analyzed using a linear mixed-effect model with baseline weight-for-age z-score, sex, age at baseline (0 to ≤ 60 days, 60 to ≤ 120 days, 120 to ≤ 180 days, > 180 days) and center included as fixed effects. Random effect will be the subject. Non-inferiority will be concluded if the lower bound of the two-sided 95% confidence interval (CI) of the mean difference in weight-for-age z-score after 4 months of intervention between Test group and Control group is more than −0.5 z-scores (non-inferiority margin). Such procedure corresponds to a one-sided testing at 2.5% level. For secondary endpoints, continuous variables (anthropometrics, IGSQ score, CoMiSS score, stool consistency and energy and macronutrient intake) will be compared between groups using a linear mixed-effect model. Stool frequency as a count variable will be compared between the groups by a generalized model approach. All secondary endpoints models will include baseline measurement, sex, age at baseline, and center as covariates. Random effect will be the subject (wherever applicable). Secondary endpoints comparisons will be performed using two-sided tests at 5% level. Occurrence of adverse events will be summarized in a table presenting frequency, severity, seriousness of adverse events, as well as their relationship to the assigned formulas.

Data will be entered from the source document into an electronic Case Report Forms by the investigators. Data quality will be regularly monitored in a blinded way by the sponsor throughout the study. Where required, queries will be sent to the sites, and all data modifications will be documented in an audit trail file.

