#### Sample size

2.2.1

The sample size calculation is based on the reported weight-for-age z-score after 4 months of formula feeding in a similar study in infants with CMA (27). To demonstrate non-inferiority with 90% power, a non-inferiority margin of - 0.5 z-score and *α*-level of 0.05, 36 infants would be needed per group. This calculation assumes that the control group would have growth rate that is 0.03 z-score slower than the test group due to a slightly lower protein content in the control formula. Assuming a drop-out rate of 30%, a total sample size of 104 infants (52 infants per group) will need to be recruited to have 72 completers (36 per group).

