#### Primary outcome

2.4.1

The primary outcome is weight-for-age z-score after 4 months of intervention. The treatment difference between the Test formula and Control formula will be estimated by a linear mixed-effect model. Fixed effects will include baseline weight-for-age z-score, age at baseline (0 to ≤ 60 days, 60 to ≤ 120 days, 120 to ≤ 180 days, > 180 days) and center. Random effect will be the infant. Primary analysis will be in the per-protocol (PP) dataset. Weight-for-age z-score after 4 months of test formula intake will be at least as good as the control, if the treatment difference between the Test group (HRF-HMO) and Control group (eHF-HMO) is < −0.5 SD (non-inferiority margin) (29). The treatment difference is superior to −0.5 SD if the lower bound of the two-sided 95% confidence interval is more than −0.5 SD. Such procedure corresponds to a one-sided testing at 2.5% level.

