##### Growth assessment

2.4.2.1

Growth outcomes include weight-for-age, length-for-age, head circumference-for-age, weight-for-length and BMI-for-age z-scores, as well as tibia and femur length. Weight and length will be collected at enrollment and monthly throughout the study, while head circumference, tibia and femur length will be measured at baseline and at 4 months post-intervention. Anthropometry parameters will be measured using standardized methodology and calibrated instruments by trained personnel. Weight, length and head circumference measurements will be performed two times by two trained persons, to the nearest 10 g, 0.1 cm and 0.1 cm respectively; they will then be plotted against the WHO Growth Standards. Tibia length corresponds to the distance between the tip of the medial condyle and the tip of the medial malleolus. Femur length is the distance between the tip of the greater trochanter and the lowest point of the lateral condyles. Both measurements should be taken three consecutive times, to the nearest 0.1 cm in a lying position using a tape measure.

Considering that complementary food intake may affect growth outcomes, dietary intake will be evaluated through 24-h dietary recalls conducted at baseline, as well as at the 2 and 4-month visits. This assessment aims to determine the type and quantities of all foods and beverages consumed by the infant. Investigators will receive detailed instructions and training to ensure accurate recording of complementary food intake.

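### Both populations that test the primary endpoint require a month-4 weight, so the weights of infants who leave early go unused and agreement between FAS and PP cannot reveal growth-related drop-out

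*Protocol article*

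**What the plan says.** The protocol article fixes the following.

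- **FAS (2.4.4, Data analysis):** "The full analysis set (FAS) will consist of a subset of subjects from the ITT with available weight-for-age z-scores at baseline and 4 months". Complete model covariates are also required.
- **PP set (2.4.4):** "The Per Protocol (PP) set will include all infants from the FAS having no protocol deviations impacting the primary endpoint". Any condition for entering the FAS is therefore also a condition for entering the PP set.
- **Primary set (2.4.1, Primary outcome):** "Primary analysis will be in the per-protocol (PP) dataset".
- **Sets used for endpoints (2.4.4):** "The primary and secondary endpoints will be analyzed in both FAS and PP populations".
- **ITT set (2.4.4):** "The Intention-to-Treat (ITT) analysis population will include all randomized infants". No endpoint analysis is assigned to it.
- **Weights available (2.4.2.1, Growth assessment, and Table 2):** "Weight and length will be collected at enrollment and monthly throughout the study".
- **Model (2.4.4):** a linear mixed-effect model; "Random effect will be the subject".
- **Drop-out (2.2.1, Sample size):** "Assuming a drop-out rate of 30%, a total sample size of 104 infants (52 infants per group) will need to be recruited".

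**The concern.** Being weighed at month 4 is a post-randomization event, and both sets that test the primary endpoint are conditional on it. An infant who leaves after month 3 has four of the five scheduled weights on file and contributes none of them to the test.

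A completer analysis is safe if leaving is unrelated to growth. That is hard to take for granted here. The Discussion describes growth problems as common in cow's milk allergy, including during the elimination diet, and poor gain on the assigned formula is a natural reason to stop. If slow growers leave more often and the test arm grows more slowly, the test arm loses more of its worst growers and the estimate drifts toward non-inferiority.

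In a non-inferiority trial, agreement between FAS and PP is the usual reassurance. Here both sets lack the same infants, so agreement says nothing about this form of attrition. The mixed model could use partial series, but the population definition removes the infants for whom that matters. A random infant effect has a use only if several visits per infant enter the model. Even if completers' interim weights do enter, those of the infants who left do not.

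**Working it through.** **1. The plan's own figure.** 36/0.70 = 51.4, rounded up to 52 per group, so 104 in total. 104 × 0.70 = 72.8, so the 72 completers remain. The stated figure reproduces exactly. About 104 × 0.30 = 31 infants would have no month-4 weight.

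**2. SD (assumed).** The article gives none. Back-solving from 36 per group, 90% power, margin 0.5, expected difference +0.03 and a one-sided 2.5% test:

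SD = 0.53 × √18 / (1.960 + 1.282) = 0.694 (0.684 with a t-based formula).

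If the 0.05 in section 2.2.1 was one-sided, the SD would be 0.768. The simulations below use 0.69.

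**3. Power with completers only.** SE = 0.694 × √(2/36) = 0.1636. Then 0.53/0.1636 − 1.960 = 1.280, which gives 90.0%. This is the planned power.

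**4. Power with all weights.** Assume equal, independent monthly changes (a random walk) and 8.5% leaving per month, so that 1 − 0.915⁴ = 29.9% leave.

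- The fractions still present at months 1 to 4 are 0.915, 0.837, 0.766 and 0.701.
- Each monthly change is estimated from the infants still present, so the effective fraction is 1 / [0.25 × (1/0.915 + 1/0.837 + 1/0.766 + 1/0.701)] = 0.797.
- The effective number is 52 × 0.797 = 41.4 per arm, and SE = 0.694 × √(2/41.4) = 0.1525.
- 0.53/0.1525 − 1.960 = 1.515, which gives 93.5%.

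Simulation gives 88 to 89% for completers (estimated SE, t cut-off) and 93% with all weights, so the gain is roughly 4 points. Over month-to-month correlations of 0.5 to 0.95 and three drop-out timings, the effective number is 37 to 51 per arm and power is 91 to 97%, a gain of 1 to 7 points.

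**5. Bias (assumed scenarios).** 52 per arm, SD 0.69, random-walk growth, about 30% leaving, true difference exactly −0.5. The odds of leaving are doubled or tripled per 0.5 z lost. The ranges cover separate simulation runs.

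| Growth-driven leaving | Completer estimate (doubled / tripled) | False non-inferiority (nominal 2.5%) |
|---|---|---|
| Same rule in both arms | −0.47 / −0.44 | about 4% / 5 to 6% |
| Test arm only | −0.39 to −0.40 / −0.31 to −0.36 | 9 to 10% / 14 to 21% |

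The estimate using all weights stayed at −0.49 to −0.50, with 2.4 to 2.9%.

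The first row depends on how drop-out is calibrated. Under the same rule, the slower-growing arm loses more infants. A further run of 4,000 trials per scenario held drop-out at 30% in each arm separately; the shift then fell to about 0.01 to 0.02 z, with false non-inferiority of 2.4 to 3.0%.

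**6. A second route for the one-arm case.** Suppose 30% of test infants leave after month 2 and the lightest are more likely to go (logistic slope 1.5 per SD). The completer mean of the test arm is then too high by 0.11 z (correlation 0.7) to 0.18 z (correlation 0.9), which is 22 to 37% of the 0.5 margin.

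**The case against.** The strongest case on the other side has five parts.

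- **Power.** A reader might infer that the definition costs the trial its power. It does not: section 2.2.1 sizes the trial on 72 completers. What is forgone is optional precision. This objection stands in full.
- **The bias figures are stress scenarios.** They need a true deficit at the margin and leaving driven by growth. The largest also need that leaving in the test arm only. Nothing in the article points to arm-specific drop-out, and the plan expects the test arm to grow 0.03 z better. This stands: the figures show what the design could not detect, not what will happen.
- **The good behaviour of the all-weights analysis is built in.** Leaving was driven by recorded weights, so data were missing at random, and pass rates used the estimator's empirical SD. The simulations also left out center, which the plan fits as a fixed effect across 19 centers. This stands, and it is why a sensitivity analysis is needed as well.
- **The FAS is still a check on the PP set, and drop-outs are not invisible.** An infant who stops the formula but is weighed at month 4 stays in the FAS, so it does test for non-adherence. Descriptive tables by visit and group are not restricted to completers, and the safety set needs no month-4 weight. This stands, but none of it feeds the non-inferiority decision.
- **Not every drop-out has weights to recover.** Infants who leave before month 1 have none. At 8.5% per month they are 8.5/29.9 = 28% of drop-outs. The 30% is itself a planning assumption.

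Model details may be left to an analysis plan that is not shown. The population rule is stated in the article, so the finding does not rest on an omission.

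**Conclusion.** The point holds as a bias concern. By stated definition, every between-group analysis of the primary endpoint is completer-only, the monthly weights of infants who leave after month 1 are unused, and FAS–PP agreement cannot reveal growth-related attrition.

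Its size is moderate and conditional: 0.03 to 0.06 z toward non-inferiority if the same growth-driven rule acts in both arms, less if total drop-out is equal between arms, and about 0.1 to 0.2 z if it acts in the test arm only. All of this rests on an assumed SD of about 0.69, random-walk growth (an autoregressive pattern for the second route in the one-arm case) and invented drop-out rules. The forgone power of roughly 4 points is secondary.

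Two stronger readings are not supported: that the trial falls short of its planned 90% because of this rule, and that its result will be biased. The change should be made, but it is not a fatal flaw.

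**What to change.** In section 2.4.4:

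1. Define the FAS for growth endpoints as all randomized infants with a baseline weight and at least one post-baseline weight.
2. Fit a repeated-measures mixed model to the month 1 to 4 z-scores, with treatment, visit, treatment-by-visit and the listed covariates.
3. Keep the decision rule: the month-4 treatment contrast and its 95% CI against −0.5.
4. Keep the present completer set under its own name, draw the PP set from it as now, and keep both analyses as planned. The PP set need not be redefined; whether to use its weights recorded while compliant is a debatable choice of estimand.
5. Add a sensitivity analysis that shifts missing test-arm month-4 values downward.

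The sponsor should settle this before unblinding. It needs no extra visits, measurements or infants, only wording, some programming and a few more covariance parameters. The new analysis relies on data being missing at random given the observed weights, which is weaker than what the completer analysis needs but still an assumption. Infants with no post-baseline weight stay outside the model.

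### Both analysis sets for the primary endpoint require a 4-month weight, so neither can show whether the non-inferiority conclusion is robust to the planned drop-out

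*Protocol article*

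**What the plan says.** Section 2.4.4 (Data analysis) defines the ITT population as everyone randomised. It then restricts the FAS to "a subset of subjects from the ITT with available weight-for-age z-scores at baseline and 4 months", with complete covariates. The PP set is drawn from the FAS and also removes infants with relevant deviations, including non-compliance with feeding. On which sets carry the endpoints, the section says: "The primary and secondary endpoints will be analyzed in both FAS and PP populations". Section 2.4.1 (Primary outcome) settles the order: "Primary analysis will be in the per-protocol (PP) dataset". The ITT population is the parent of the FAS and of the safety set, but no growth analysis is assigned to it.

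Three other statements bear on this:

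- Section 2.2.1 (Sample size) inflates the target for losses ("Assuming a drop-out rate of 30" per cent): 104 randomised to obtain 72 completers.
- Section 2.4.2.1 (Growth assessment) says "Weight and length will be collected at enrollment and monthly throughout the study", and Table 2 confirms weights at visits V0 to V4.
- Sections 2.4.1 and 2.4.4 specify a linear mixed model with the infant as random effect.

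**The concern.** A PP primary analysis is common in a non-inferiority trial. It is normally paired with a fuller set, so that agreement between the two says something about the infants whom the PP set leaves out. Here the fuller set has the same month-4 filter. The FAS can show whether non-compliance matters among infants weighed at month 4. It cannot show whether drop-out matters, because those who dropped out are in neither set.

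If infants who grow poorly leave the study before month 4, and more of them leave the arm that grows more slowly, those remaining in that arm look better than the arm as randomised. The estimated difference then moves toward zero, which favours a non-inferiority claim. The filter also discards the month 1–3 weights of the infants for whom those weights are most informative. A subject random effect presupposes several records per infant, so the chosen model could use them.

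**Working it through.** **1. The plan's own figures.** 36 / 0.70 = 51.4, rounded up to 52 per group, 104 in total, as stated. Planned loss: 104 − 72 = 32, and 32/104 = 30.8%. The PP set can only be smaller than the FAS.

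**2. An SD to work with.** The article gives none. Its inputs are "To demonstrate non-inferiority with 90% power", "a non-inferiority margin of - 0.5 z-score", "level of 0.05, 36 infants would be needed per group", and an assumed advantage of 0.03 for the test formula. With n = 2(z₁₋α + z₀.₉)² SD² / (0.5 + 0.03)²:

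- One-sided 2.5% (the level of the planned 95% CI), SD 0.69: 2 × (1.960 + 1.282)² × 0.69² / 0.53² = 35.6, so 36.
- One-sided 5%: the largest SD that still gives 36 is about 0.77.

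SD 0.69 is used below. It is a back-solved assumption, not a figure from the article.

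**3. How far apart the missing infants would have to be.** The half-width of the 95% CI with 36 per group is 1.96 × 0.69 × √(2/36) = 0.32. Non-inferiority therefore needs a point estimate above about −0.18. If 30% are missing in each arm and completers differ by c, the all-randomised difference reaches −0.5 when the missing infants differ by (−0.5 − 0.7c)/0.3. This is −1.67 for c = 0 and −1.20 for c = −0.2. A gross reversal would thus need a large difference among those lost. Bias can also arise from unequal loss, which step 4 covers.

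**4. Simulation at the margin.** Assumptions: 52 per arm; true month-4 difference −0.5, diverging linearly; SD of 4-month change 0.69, built from independent monthly increments; drop-out after months 1, 2 or 3, with log-odds depending on weight change so far by the same rule in both arms; overall drop-out about 30%; 5,000 trials per row. The completers' estimate adjusts for baseline. The alternative is a likelihood estimate from every available monthly weight.

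| Dependence of drop-out on poor growth | Drop-out, test / control | Completers' estimate | False non-inferiority | All-weights estimate |
|---|---|---|---|---|
| None | 31% / 31% | −0.50 | 3.2% | −0.50 |
| Moderate | 35% / 26% | −0.46 | 4.4% | −0.50 |
| Strong | 37% / 23% | −0.41 | 8.6% | −0.50 |

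The nominal rate is 2.5%. The first row is slightly above it because 1.96 was used in place of a t quantile, and because of simulation error. One common rule produces unequal loss here because the test arm is, by construction, growing more slowly.

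**5. Variations** (SD rising from 0.35 to 0.69, adjacent-visit correlation 0.9, true difference −0.5):

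- Drop-out held at 30% in each arm with equal dependence on growth: estimate about −0.50, false non-inferiority 2.7–2.9%.
- Growth-driven drop-out in the test arm only: estimate from −0.41 to −0.24, false non-inferiority from 8% to 38%, depending on strength. The top value also lets drop-out exceed the planned 30%.

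**6. Precision.** With drop-out unrelated to growth, the estimator SD was 0.1625 for completers and 0.144 for all weights: (0.144/0.1625)² = 0.785, a variance 21% lower. Under the step 4 structure it was 0.168 and 0.153: ratio 0.829, 17% lower. Conversely, the completers' variance is 21–27% higher. With strong growth dependence the two SDs were equal (0.155), so the gain there is in bias only.

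**The case against.** The strongest reply is that a PP primary analysis with a supporting FAS is a recognised non-inferiority design, and that missing-data handling usually belongs in the SAP. The first part stands: the choice of PP as primary is not the fault. The second does not rescue the FAS, because the article itself fixes the month-4 requirement and names the two sets that carry the endpoints.

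Several stronger readings are tempting, and the document does not support them.

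- A reader might infer that the plan has a false-positive rate near 38%. That needs growth-driven drop-out in the test arm and none in the control arm. The article gives no reasons for drop-out and no sign of such asymmetry. Parents, investigators and site staff are blinded (section 2.2.2), though section 2.3.2 admits minor taste differences.
- A reader might infer that every infant who refuses or does not tolerate the formula vanishes. An infant who stops the formula but is weighed at month 4 stays in the FAS and may leave only the PP set.
- A reader might infer that 30% will be lost. That is a planning figure.
- A reader might infer that safety is also restricted to completers. The safety set covers every randomised infant with at least one documented product administration. This does not repair the growth estimate.
- A reader might infer that an all-weights model is unbiased whatever the cause of loss. In these simulations drop-out depends only on weights already observed, which is the condition under which that model is valid. If infants leave because of weight change after their last visit, it is biased too.

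**Conclusion.** The point holds in limited form. By its stated definitions, the plan has no analysis of the primary endpoint that includes an infant without a 4-month weight, and the supporting set cannot test robustness to drop-out. If drop-out is unrelated to growth, the cost is precision alone. If it depends on growth but is balanced between arms, no bias appeared. If poor growth drives drop-out and the slower-growing arm loses more infants, false non-inferiority at a true difference of −0.5 is roughly 4–9% against a nominal 2.5%; larger values belong to worst cases confined to the test arm. These figures rest on a back-solved SD, an assumed correlation structure and assumed drop-out mechanisms, none of which the article gives. They show direction and order of magnitude, and do not predict this trial's error rate. The change is a worthwhile, inexpensive improvement; nothing here shows that the planned conclusion would be wrong.

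**What to change.** Redefine the FAS as all randomised infants with a baseline weight-for-age z-score and at least one post-baseline weight, analysed as assigned. Fit the mixed model to months 1–4 with visit and treatment-by-visit terms, the covariates already planned, and an unstructured or similar within-infant covariance. Report the month-4 contrast and its 95% CI against −0.5 next to the PP result. State that this is valid if drop-out is explained by the observed weights. Infants with no post-baseline weight would still be outside the set and should be counted by arm.

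The cost is a change of wording and a little programming, with no added infants, visits or measurements. The drawback is a supporting analysis that may disagree with PP and would then have to be discussed. Requiring success in both sets, or adding a delta-shift sensitivity analysis, is optional: the first is a design preference that makes success somewhat harder, and the second can sit in the SAP.

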##### Gastrointestinal tolerance

2.4.2.2

To assess gastrointestinal (GI) tolerance to study formulas, the Infant Gastrointestinal Symptom Questionnaire (IGSQ) will be administered at each visit and via a phone call after the first week of study formula use. IGSQ is a validated questionnaire including 5 symptom clusters, yielding a 13-item index of parent-reported infant digestion and elimination behaviors over the prior 7 days (30). It is the most commonly used tool to assess infant GI-related symptoms in clinical studies. During the first week of the study period, a daily gastrointestinal tolerance questionnaire will also be completed by the parents, including questions on the presence and severity of flatulence, vomiting, crying, fussing and sleep duration.

The Brussels Infant and Toddler Stool Scale, a validated stool scale, will be used to assess stool consistency (31). Parents will document stool frequency and consistency (categorized as watery, loose, formed, or hard) in a diary over three consecutive days prior to the 2- and 4-month visits, along with a one-day retrospective record of stool frequency and consistency at baseline.

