##### Allergy symptoms

2.4.2.3

Assessment of allergy symptoms will be conducted at baseline and each visit using the Cow’s Milk-related Symptom Score (CoMiSS) (32). CoMiSS is a validated awareness tool for CMA and includes possible manifestations of CMA such as skin, GI, respiratory and general symptoms. CoMiSS can also be used to evaluate and quantify the evolution of allergy symptoms, with scores ranging from 0 to 33.

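### Tolerance and allergy-symptom scores already recorded are left out of the group comparisons when an infant has no 4-month weight

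*Protocol article*

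**What the plan says.** Section 2.4.4 (Data analysis) defines four sets and assigns endpoints to two of them.

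- ITT: "The Intention-to-Treat (ITT) analysis population will include all randomized infants". No analysis is assigned to it.
- FAS: a "subset of subjects from the ITT with available weight-for-age z-scores at baseline and 4 months", who also have the model covariates.
- PP: drawn from the FAS, with further exclusions; in particular, "infants that are non-compliant to feeding interventions will be excluded from the PP set".
- Safety set: "all infants in the ITT population with documentation of at least one administration of study product", analysed by product received. No endpoint is explicitly assigned to it.

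The assignment reads "The primary and secondary endpoints will be analyzed in both FAS and PP populations".

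Gastrointestinal tolerance and allergy symptoms are secondary objectives (Introduction). Section 2.4.2.2 says that the IGSQ "will be administered at each visit and via a phone call after the first week of study formula use". Section 2.4.2.3 says of the CoMiSS: "Assessment of allergy symptoms will be conducted at baseline and each visit". Section 2.4.4 plans linear mixed models for IGSQ, CoMiSS and stool consistency, and a generalised model for stool frequency.

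**The concern.** A 4-month weight is needed to analyse 4-month weight. It has no bearing on whether a day-7 IGSQ or a month-1 CoMiSS is valid. The article nevertheless makes it the entry condition for analysing those scores too.

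Having that weight is a post-randomisation event that the assigned formula may influence. Vomiting, crying and allergic symptoms are what these instruments record, and they are plausible reasons for a family to leave. Selecting on such an event gives up the protection of randomisation for these endpoints. Because PP is nested in the FAS, both analyses share the selection, so agreement between them would not be independent reassurance. At stake is a named part of the trial's purpose: to learn whether the new formula is well tolerated.

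**Working it through.** **1. The plan's own figure.** Section 2.2.1 gives 36 completers per group and "Assuming a drop-out rate of 30" per cent. Then 36 / (1 − 0.30) = 51.4, rounded up to 52 per group, and 2 × 52 = 104. This reproduces the stated total. Completers are 2 × 36 = 72.

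**2. Ceiling on the infants affected.** 104 − 72 = 32, or 16 of 52 per group; 32/104 = 30.8%. This is a ceiling at the planned rate because:

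- the 30% covers drop-out for any reason, without timing, and an infant who leaves before any post-baseline score has none to lose;
- the 36 per group serves a primary analysis in PP (Section 2.4.1), so the 30% may also cover PP exclusions of infants who do have a 4-month weight.

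**3. What can be left out for an infant with no 4-month weight** (Table 2 and Section 2.4.2.2).

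| Endpoint | Post-baseline times | Times before month 4 |
|---|---|---|
| IGSQ | day 7, months 1, 2, 3, 4 | up to 4 |
| CoMiSS | months 1, 2, 3, 4 | up to 3 |
| 3-day stool diary | months 2, 4 | up to 1 |

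The week-1 daily questionnaire is also collected early, but it is not among the models listed in Section 2.4.4. Quality-of-life questionnaires are scheduled only at baseline and month 4, so they have no intermediate scores to lose.

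**4. Would the mixed model recover these data?** A mixed model with the infant as random effect can use early visits from infants who later leave. Here the FAS condition removes those infants before the model is fitted.

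**5. How a difference can disappear.** The figures in this step are assumptions, not from the article. Suppose 10% of infants who do not leave for intolerance have marked early symptoms in each arm. Suppose also that every infant who leaves for intolerance has such symptoms recorded and has no 4-month weight. With x such leavers, the rate among all 52 is (0.10 × (52 − x) + x) / 52.

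| Leavers, test v control | All randomised, test | All randomised, control | Difference | FAS difference |
|---|---|---|---|---|
| 4 v 4 | 8.8/52 = 16.9% | 8.8/52 = 16.9% | 0 | 0 |
| 8 v 4 | 12.4/52 = 23.8% | 8.8/52 = 16.9% | 6.9 points | 0 |
| 12 v 4 | 16.0/52 = 30.8% | 8.8/52 = 16.9% | 13.8 points | 0 |

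The FAS column is zero by construction, since the remaining infants are assumed alike. The table shows the mechanism and does not estimate the bias. Swapping the arms hides a difference of the same size in the other direction, and equal losses hide nothing.

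**The case against.** Several points on the other side stand, and they limit the reach of the concern.

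- **Stopping formula is not the same as lacking a weight.** A reader might infer that every infant who stops for intolerance is removed from the tolerance analysis. The article does not support that: FAS membership turns on the 4-month weight and covariates, so an infant who stops but attends the last visit stays in. Whether such infants are followed to month 4 is not stated, and an article may leave that to the full protocol.
- **A switch of formula does not by itself mean exclusion from PP.** Section 2.4.2.5 sets an 85% compliance threshold. Read as a share of days over roughly 120 days, it allows 0.15 × 120 = 18 non-compliant days, so a late switch may be tolerated.
- **Intolerance has another reporting route.** Adverse events are sought at each visit and call and tabulated with their relationship to formula, presumably in the safety set. Descriptive statistics by visit and feeding group are planned without a named set. The loss is certain only for the FAS and PP comparisons.
- **Precision is limited in any case.** Without adjustment, the standard error of a standardised mean difference is √(2/52) = 0.196 SD with all infants, against √(2/36) = 0.236 SD with completers. Modest differences would often be missed either way. That concerns power and does not remove a selection bias.

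An unseen SAP is not an answer, because the article itself fixes both the set definition and its use for secondary endpoints.

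**Conclusion.** The point holds in limited form. As written, IGSQ and CoMiSS scores, and any month-2 stool diary, from infants with no 4-month weight are excluded from the planned between-group comparisons. At the planned drop-out this concerns at most 32 of 104 infants (31%), and fewer under either condition in step 2. It would be wrong to infer that 32 infants will lose early data, or that the trial cannot show intolerance at all.

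Bias towards no difference rests on two assumptions that the article neither confirms nor excludes: that poor tolerance contributes to leaving without a 4-month weight, and that it does so unequally between arms. Its size and direction cannot be stated without drop-out reasons by arm. The primary non-inferiority test on weight and the sample size are untouched. The change should be made, but the trial's main conclusion does not depend on it.

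**What to change.** In Section 2.4.4:

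1. Apply the 4-month-weight condition to the primary endpoint only.
2. Analyse IGSQ, CoMiSS and stool endpoints, and the week-1 questionnaire if it is compared, by assigned formula. Include all randomised infants with at least one administration of study product and at least one post-baseline value of that endpoint, and use all available visits in the planned models.
3. State how scores recorded after a switch of formula are handled. Otherwise, scores on and off study formula are mixed, which can itself dilute a difference in tolerance.
4. Keep PP as supportive for these endpoints.
5. Beside these results, report by arm the number of infants who stopped study formula for intolerance or allergy symptoms.

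The cost is a wording change before unblinding, with no new data, visits or infants. At the planned drop-out, up to 104 infants rather than about 72 become eligible for these comparisons. The small downside is that denominators differ between the weight endpoint and the tolerance endpoints, which table footnotes can explain.
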